## Abstract

**Background:**

Risk perception plays an important role in decision-making processes. Differences in obstetric intervention rates suggest that, in addition to medical indications, the risk perception of obstetric health professionals might have a major influence on their decision-making process during childbirth. Although studies have investigated whether risk perception affects the role of midwifery or influences decision making during childbirth, little is known about what obstetric health professionals actually perceive as risk or risky situations and whether different risk perceptions lead to more interventions during intrapartum care.

**Objective:**

The objective of this study is to understand the association of risk perception and the decision-making processes of obstetric health professionals (midwives and obstetricians) in Germany during intrapartum care. The study has 3 specific aims: (1) gain insight into what obstetric health professionals perceive as risk in the German clinical setting, (2) assess the extent to which personal and systemic factors have an impact on obstetric health professionals’ risk perception, and (3) investigate whether different perceptions of risk are associated with different decisions being made by obstetric health professionals.

**Methods:**

This is an exploratory sequential mixed methods study with 2 phases, a qualitative followed by a quantitative phase. In the first phase, qualitative data are collected and analyzed by conducting focus group discussions and applying qualitative content analysis to address aim 1. In the second phase, for aims 2 and 3 and to help explain the qualitative results, quantitative data are collected and analyzed by conducting an observational study using case vignettes within a survey constructed on the basis of the qualitative results.

**Results:**

Enrollment in the first (qualitative) phase began in July 2019, and data collection and analysis have been completed. The second (quantitative) phase is currently planned, and data collection is expected to start in December 2020. First results of the qualitative phase are expected to be submitted for publication in 2020, with completion of the second phase scheduled for 2021.

**Conclusions:**

This mixed methods study will examine the perception of risk and its association with the decision-making processes of obstetric health professionals during their care of women in childbirth. The rationale for this approach is that the qualitative data and their analysis explore participants' views in more depth, while the quantitative data will help to provide and explore a general understanding of the research problem. The results are expected to be relevant to health care professionals, policymakers, and educational institutions in order to minimize underuse, overuse, and misuse of interventions during intrapartum care.

**Trial Registration:**

German Clinical Trials Register DRKS00017172; https://tinyurl.com/y2zoowkx

**International Registered Report Identifier (IRRID):**

DERR1-10.2196/21443

## Introduction

### Background

Professionals in the field of childbirth have to make many decisions daily regarding the births they are involved in. These decisions can have far-reaching consequences for the women and children involved. They concern in particular the application and implementation of interventions during intrapartum care which have become routine in developed countries, although their effectiveness is often unproven [1]. A large number of women experience some form of intervention during labor, for example, an epidural, administration of oxytocin, an episiotomy, or a caesarean section [2,3]. However, there are remarkable major cross-national and regional differences [3-7]. For example, in 2017 the caesarean section rates in Europe ranged from 15% to 37% [8], and an even larger range of 5%-70% was found for episiotomy [8]. Clear reasons for these differences are not known [9,10]. Aside from the lack of knowledge about the effectiveness of many interventions [1,11], forensic reasons are assumed to influence the decision regarding whether or not to intervene [5,12]. Maternity care is labeled as “risk oriented” and different risk assessments are considered to be the reason for the differences in intervention rates [5]. The fear of litigation “has led to a rising level of intervention in labour” [13] and it influences health professionals’ decisions to perform interventions, for example, a caesarean section [12]. Therefore, this explains why the concept of risk and risk management has become a central principle in the care of women during childbirth [7].

MacKenzie Bryers and van Teijlingen [14] emphasize the importance of the “cultural influences, or the way risk is perceived” in provision of maternity care and refer to Downe [15], who argues that social and environmental issues such as institution, experience, and environmental impact are also important. In general, risk perception refers to subjectively perceived risk, that is, the subjectively perceived probability of the occurrence of a normally negative event [16]. Therefore, risk perception is “highly subjective” and a complex process [17]. Studies on risk perception and decision making show that nonlinear weighting of probabilities, heuristics (eg, availability or anchoring heuristics), and systematic biases play a role in risk perception [18,19]. Simplified rules of thinking and decision making lead to hasty judgments and systematic deviations between perception and reality. In addition, medium and high probabilities are often underestimated, while the occurrence of events with a lower probability are often overestimated [18,19]. Nevertheless, adequate risk perception of health professionals in maternity care is important, so that both trivialization and overestimation of risks do not lead to an inappropriate care, that is, to overuse, underuse, or misuse of interventions in labor. The significant differences in intervention rates may indicate that this is currently the case without it being possible to judge whether there is too little, too much, or adequate willingness to intervene in some regions and areas [3].

Mead and Kornbrot [20] investigated the influence of maternity units’ intrapartum intervention rates and the risk perception of midwives. The authors stated that there is a relationship between practice and perception of midwives, and that midwives working in a unit with high levels of intrapartum intervention generally had a higher perception of risk than those working in a unit with a lower intervention rate. Healy et al [21] used semistructured interviews to investigate whether midwives’ and obstetricians’ perceptions of risk affected care practices for normal birth and low-risk women in labor. They state that birth is viewed through the lens of medicalization and they consider this the reason for the routine use of interventions and technology. Researchers from the Netherlands [13,22] examined the association between a midwife’s personality, place of work, years of experience, and the timing of their decisions to make referrals from primary midwifery care to secondary obstetric care using case scenarios (vignettes). The authors found no significant correlations and stated that other factors must explain the variations in referral decisions. Nevertheless, they claim that “risk perceptions or beliefs about the course of labour influence midwives’ decisions” (p. e76). However, the transfer of these results to the German health care context is limited due to the different models of care available for women in labor.

In Germany, in general, midwives and obstetricians are involved in the care of women giving birth. According to the legal regulations, a midwife must be present at every birth and therefore all women in labor, regardless of having a low- or high-risk pregnancy, are cared for by midwives. In a low-risk birth without complications the midwife is responsible for the birth process on her own; nevertheless, in hospitals a doctor usually is also present at the actual birth. In a high-risk birth or when abnormalities occur, a doctor must be called and takes charge of the birth, but a midwife still takes care of the woman. There are some midwife-led units where women in labor with a low-risk pregnancy are cared for exclusively by midwives as long as no abnormalities occur [23], but this is rather the exception. However, most births occur in consultant-led obstetric units [2]. Therefore, women giving birth in hospitals are usually interdisciplinary cared for by midwives and obstetricians. Decisions to or not to intervene are made by a midwife alone, by a doctor alone, or together, which depend on the model of care and the circumstances. In Germany, there also are regional variations in the use of interventions. For example, the overall caesarean section rate was 30.2% in 2015 [24], but varied from 19% to 47% in western and eastern districts of Germany [5,6]. Epidurals and augmentation of labor differed significantly in hospitals with lower or higher annual number of births [25]. The high intervention rates and the regional differences lead to the assumption that, in addition to medical indications, other factors influence the decision to intervene. As other researchers showed, these might be the clinicians' personal beliefs, including the risk perception, which was an influencing factor for the choice of the mode of birth, of performing a cesarean section [12]. The association between risk perception and the decision-making processes of health professionals during intrapartum care has not yet been investigated in the German clinical setting. To gain insights into the decision making to use interventions during childbirth is of importance to study because interventions such as administering an epidural agent, intrapartum use of oxytocin, performing an episiotomy or a caesarean section are associated with short- and long term effects such as higher maternal mortality and morbidity (eg, increased risk of uterine rupture, abnormal placentation, sexual dysfunction), less satisfaction with the birthing process, a longer and more costly hospital stay, a longer recovery including the experience of pain and reduced mobility, or stillbirth, preterm birth, and greater incidence of late childhood obesity [7,26-30]. This has led to the tremendous increase in the relative cost of birth within the last century; besides, obstetric interventions during labor for women with a low-risk pregnancy, in general, are costly to the health system [31].

It is therefore crucial to gain insight into the risk perception of obstetric health professionals working in Germany so as to investigate the association between risk perception and decision-making processes in the German clinical setting in order to improve intrapartum care in Germany. Overall, in a simplified view, midwives and obstetricians are often assigned to different models of care, with midwives being assigned to the social model focusing on normality and obstetricians to the medical model focusing on technology and pathology. Although more of a continuum, this could be an indication of different approaches and perspectives due to socialization [14]. Therefore, this work focuses on the risk perception of obstetric health professionals in general, but differentiates between midwives and obstetricians to obtain more specific insights.

### Aims and Research Question

The overall aim of this study is to understand the association between risk perception and the decision-making processes of obstetric health professionals in Germany during intrapartum care. This study has 3 aims: (1) to gain insight into what midwives and obstetricians perceive as risk in the German clinical setting in order to construct valid case vignettes of risky situations; (2) to assess the extent to which personal factors (eg, age, gender, professional experience, qualification level) or systemic factors (eg, annual number of births or level of care provided, ie, secondary or tertiary) have an impact on midwives’ and obstetricians’ risk perception; and (3) to investigate whether differing perceptions of risk are associated with different decisions by midwives and obstetricians.

To this end, the research questions are as follows:

1. What do obstetric health professionals understand by risk in labor in a clinical setting, and which situations are perceived as risky intrapartum?

2. Do personal, systemic, or both factors affect the risk perception of obstetric health professionals?

3. Does risk perception affect the decisions of the obstetric health professionals or the care of women in labor?

The decisions were predefined as administering an epidural agent, intrapartum use of oxytocin, or performing an episiotomy or an unplanned caesarean section. However, adding other decisions based on the results of the first research question remained open.

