#### Data Collection and Statistical Analysis

Participants will be asked to fill out a version of either the web-based or paper-and-pencil self-constructed survey containing the vignettes of different birth scenarios. The primary endpoint is the risk perception of obstetric health professionals (midwives and obstetricians) caring for women giving birth measured on a 6-point Likert scale. The primary endpoint is thus ordinally scaled with 6 parameter values (from 0=hardly or no risk to 5=very high/highest possible risk).

As the aim is to invite as many midwives and obstetricians to participate as possible, no formal statistical sample size calculation will be carried out.

The secondary endpoint is the decision to intervene (binary with the variables “intervene yes” and “intervene no”) whereby the decisions are partly predefined as described earlier. On the basis of a 5-point Likert scale (from 1=very unlikely to 5=very likely to choose the intervention), if the score is over 3, the characteristic “intervene yes” will be assumed.

Descriptive presentation of the results of the primary endpoint (categorical; 6 categories) will be displayed through bar charts and associated absolute and relative frequencies. Other additionally recorded variables will be analyzed according to the data situation (continuous, categorical, or binary) using statistical methods appropriate to the data structure (categorial/binary: absolute and relative frequencies; continuous: medians, quartiles, means, standard deviation, minimum, maximum). Exploratory analyses for the primary endpoint (generating hypotheses) will be performed via ordinal regression using SPSS (IBM Inc) or R (R Foundation for Statistical Computing) with the following potential influencing factors: age, gender, type of professional qualification, years of experience, annual number of births or level of care of the current work location, and personality inventories. The choice of the link function to be used for this purpose will depend on the distribution of the observed cases among the different categories of the dependent variable. The quality of the model will be checked by Nagelkerke R^2^. Results of the ordinal regression will be summarized via regression coefficients, corresponding odds ratios, and by determining 95% confidence intervals for the odds ratio.

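### The predefined decisions omit calling the obstetrician and the aim 3 regression names no profession term, so its pooled odds ratio may describe neither midwives nor obstetricians

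*Protocol article*

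**What the plan says.** All references are to the protocol article.

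- **Decisions.** Aims and Research Question: "The decisions were predefined as administering an epidural agent, intrapartum use of oxytocin, or performing an episiotomy or an unplanned caesarean section". The next sentence adds: "However, adding other decisions based on the results of the first research question remained open". The Phase II section Data Collection and Statistical Analysis repeats this for the secondary endpoint: "whereby the decisions are partly predefined as described earlier".
- **Scale.** The same section describes one 5-point scale, "from 1=very unlikely to 5=very likely to choose the intervention". A score above 3 counts as a decision to intervene. No version by profession is described.
- **Who decides.** Background: "In a high-risk birth or when abnormalities occur, a doctor must be called and takes charge of the birth". It also says: "Decisions to or not to intervene are made by a midwife alone, by a doctor alone, or together, which depend on the model of care".
- **Vignettes.** Aim 1 collects risk perceptions "in order to construct valid case vignettes of risky situations".
- **Analysis for aim 3.** A logistic regression of intervene yes/no on risk perception, with forward selection by likelihood ratio test. The adjustment variables are age, gender, type of professional qualification, years of experience, annual births or level of care, and personality inventories. Midwife versus obstetrician is not named.
- **Stated intention.** The end of the Background says that the work will distinguish midwives from obstetricians.

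**The concern.** Aim 3 relates perceived risk to decisions in both professions. By the article's own account, the authority to intervene differs between them and shifts to the doctor when abnormalities occur. For a midwife, the step that the article ties to that moment is the call to the doctor, and the predefined list does not record it.

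Take a midwife who rates a vignette as very high risk and would call at once. Without a stated role, she could honestly answer that she is unlikely to choose a caesarean section herself. She would then be coded the same as a colleague who sees no problem. Another midwife might read the item as what she would recommend, and answer that she is likely to choose it. An obstetrician with the same perception is more likely to read the item as his or her own decision.

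If this happens, the slope of decision on risk perception differs by profession because of how the item is read. One pooled slope would then mix the two, and the study could report that risk perception matters little to midwives' decisions when their risk-driven decision was not asked. An item that was never asked cannot be recovered at analysis.

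**Working it through.** **1. The sections set side by side**

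| Question | What the article gives |
|---|---|
| Is calling the doctor a predefined decision? | No; four interventions are listed (Aims and Research Question) |
| Is the list closed? | No; it can be extended from phase I (same section, and Phase II) |
| Is the call important in this setting? | Yes; it is mandatory when abnormalities occur (Background) |
| Can midwives decide on interventions? | Yes, alone or jointly, depending on the care model and circumstances (Background) |
| Does the scale fix the respondent's role? | Not as described (Phase II) |
| Does the aim 3 model contain profession? | Not as listed (Phase II) |

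**2. Could a listed covariate stand in for profession?** The nearest is type of professional qualification. The Phase I section Recruitment and Sampling explains it as vocational or tertiary education. That is at best a proxy, because midwives with a tertiary qualification would share a category with obstetricians. Under forward selection it may also not be retained. Even if it were, a main effect changes the intercept and leaves a single slope for risk perception.

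**3. Illustration of a single pooled slope.** The article states no figure to reproduce. Every input here is an assumption.

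- Rating distribution, the same in both professions: 3%, 10%, 27%, 32%, 20% and 8% for ratings 0 to 5 (mean 2.8, SD 1.19).
- Within profession: logit P(intervene) = a + b × (rating − 2.8).
- Obstetricians: a = 0, b = log 2.0.
- Midwives: a = −1, b = log 1.0 or log 0.8; share of midwives 50% or 70%.
- The pooled logistic model is fitted to the exact expected proportions, so there is no sampling error.

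Pooled odds ratio per rating point. Brackets give the range when the midwives' a runs from 0 to −2.

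| Midwife odds ratio | Share of midwives | No profession term (as written) | Profession main effect added |
|---|---|---|---|
| 1.0 | 50% | 1.40 (1.37–1.45) | 1.43 (1.37–1.58) |
| 1.0 | 70% | 1.23 (1.20–1.30) | 1.25 (1.20–1.37) |
| 0.8 | 50% | 1.26 (1.22–1.36) | 1.28 (1.22–1.46) |
| 0.8 | 70% | 1.07 (1.03–1.18) | 1.07 (1.03–1.22) |

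In every row the pooled value lies between the two true values and equals neither. Adding profession as a main effect barely changes it; only separate slopes recover 2.0 and 1.0 (or 0.8). The table shows what pooling does if the slopes differ. It is not evidence that they differ.

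**The case against.** Three stronger conclusions are tempting, and the article does not support them.

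*A reader might infer that the call to the doctor has been excluded.* It has not. The list is expressly only partly predefined, additions from phase I are allowed, and survey content can be adapted. Focus-group accounts of risky situations could well bring up the call. Clinicians and experts check the vignettes for face validity, and a think-aloud pretest with clinicians follows; either could expose a role problem. This stands, but none of these steps guarantees the item. The quoted focus-group questions ask what risk is and which situations are risky, not what the respondent would do. An added item would also leave the intervention items without a stated role.

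*A reader might infer that in most vignettes the midwife is not the one who decides.* The vignettes are not shown. A situation perceived as risky is not the same as a high-risk birth or one with abnormalities, and the rating scale starts at hardly any risk. The Background has midwives deciding alone or jointly and does not allocate the four interventions by profession. This objection stands in full.

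*A reader might infer that aim 3 demonstrably measures different things in the two professions.* The item's stem is not given in this condensed article and may specify a role. The illustration assumes the slope difference that is in question, so it cannot prove it.

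It is also fair to say that the four interventions match the study's rationale, which is variation in intervention rates, and that the survey is exploratory. That weakens the case for a referral endpoint as a necessity. It does not answer the point about the pooled model: an exploratory odds ratio that averages two unlike groups can still mislead the hypotheses drawn from it.

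**Conclusion.** The concern holds as a comparability risk that is cheap to remove. Two facts rest on the text alone: the predefined decisions contain no call or referral decision, and the aim 3 regression names no profession term or interaction despite the stated intention to distinguish the professions. That the coded decision may mean different things in the two groups is a reasonable inference from the Background's account of who decides, not something the article states.

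The size cannot be derived from the document. Under the assumptions shown, an obstetrician odds ratio of 2.0 would appear as 1.03 to 1.45 in the model as written. If the two slopes are in fact alike, this dilution does not arise. The point is a recommended improvement, not an error that invalidates the design.

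**What to change.** 1. **Analysis (Phase II, Data Collection and Statistical Analysis).** Estimate the association of risk perception with each decision separately for midwives and obstetricians, or in one model with profession and a profession-by-risk-perception interaction, both kept outside the forward selection. Report the odds ratio and 95% confidence interval for each profession.
2. **Item wording (Aims and Research Question; Phase II).** Word the intervention item so that each profession answers within its role, for example how likely the respondent is to carry out, initiate or recommend the intervention.
3. **Extra item.** Use the openness already stated to add calling or informing the obstetrician as a survey decision item for midwives, analysed separately from the four interventions. This changes only what the questionnaire records, not any clinical rule.

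Cost: one more item per vignette for midwives and a wording change before the pretest, which makes the questionnaire slightly longer. Estimates within each profession will be less precise than a pooled one. As no sample size is calculated, the article does not show by how much.
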